### Eligibility and selection criteria of study participants

In both Burkina Faso and Nepal, children enrolled in school are eligible to participate in the baseline survey if they are between 8 and 14 years old, have signed a written informed consent by their parents, guardians or teachers, and themselves assented orally.

### Data collection procedures

Four weeks prior to the study, district and village authorities, school directors and children’s parents/guardians will be informed about the forthcoming survey activities by the local survey team. They will be re-informed about the purpose and procedures of the study shortly before the start of the survey activities. Written informed consent (signed or fingerprint) will be obtained from children’s parents or legal guardians, whilst children will assent orally. It will be emphasised that participation is voluntary and that children and parents/guardians can withdraw anytime without further obligation.

In each school, a random selection of children aged 8–14 years will be enrolled until at least 55 in Burkina Faso and 44 in Nepal are reached. Moreover, at the follow-up survey, the same children will be re-assessed, who by then will be 9–15 years old. Each child will be attributed a unique identification code (ID) for the different assessments at the onset of the study. A separate household ID connected to the schoolchild’s personal ID will be given to children’s households in order to link children’s clinical data and nutritional and health knowledge, attitudes and practices (KAP) with the household characteristics. Children will thereafter be invited to provide stool and urine samples, to take anthropometric and haemoglobin (Hb) measurements and to participate in the KAP survey. In Burkina Faso, stool and urine samples will be collected on two consecutive days. In Nepal, a single stool sample will be collected, while urine samples will not be collected as urogenital schistosomiasis is not endemic. Infected, anaemic or undernourished children in all schools will be subjected to clinical, parasitological and nutritional examinations, and will be treated according to national policies.

After these assessments with children at the schools, the same enumerators in Burkina Faso will visit children’s households and will invite children’s caregivers to respond to a household questionnaire during the two survey days. In Nepal, due to the scattered locations and geographical constraints, additional enumerators will visit the children’s households during the same survey period. In both countries, trained and experienced enumerators will conduct the questionnaire surveys in local languages.

### Collection of stool and urine samples

The sampled children at the schools will be asked to provide a fresh mid-morning, post-exercise stool sample. The stool samples will be processed and analysed each day (at mid-day the latest) by experienced laboratory technicians and medical microbiologists as follows: first, stool samples will be visually examined for macroscopic appearance of adult worms, also checking the stool consistency and the presence of blood and mucus. Second, a single Kato-Katz thick smear, using 41.7 mg templates, will be prepared on a slide and examined under a microscope for the presence of eggs of *Schistosoma mansoni*, hookworm, *Ascaris lumbricoides, Trichuris trichiura* and *Hymenolepis nana*, adhering to standard operating procedures [35, 36].

Third, a formalin-ether concentration technique will be used to enhance sensitivity for the diagnosis of helminths and to detect intestinal protozoa (*Blastocystis hominis*, *Chilomastix mesnili*, *Endolimax nana*, *Entamoeba coli*, *Entamoeba histolytica*/*Entamoeba dispar*, *Entamoeba hartmanni*, *Giardia intestinalis* and *Iodamoeba bütschlii*) [37]. Approximately 1–2 g of stool will be placed in 15 ml Falcon tubes filled with 10 ml of 5 % formalin and will be examined by experienced laboratory technicians for the presence of helminths and intestinal protozoa, using an ether-concentration technique, adhering to an SOP [38]. Additionally, in Nepal, 20 mg of stool will be prepared on a single slide with the saline wet mount concentration for the microscopic detection of the same intestinal protozoa and helminths, according to SOPs [39, 40]. Furthermore, the intensity of infection will be calculated as the number of eggs per 1 g of stool (EPG) and categorised according to the WHO standard classification [41].

In Burkina Faso, children will also be asked to provide fresh, mid-morning and post-exercise urine samples, collected at the same time as the stool samples. Urine samples will be analysed for microhaematuria (biochemical marker and proxy for *Schistosoma haematobium*), using reagent strips (Hemastix; Siemens Healthcare Diagnostics GmbH; Eschborn, Germany) [42], and for the presence and number of *S. haematobium* eggs in 10 ml of urine using a urine centrifugation technique and microscopy [43]. *S. haematobium* infection will be grouped into light (< 50 eggs/10 ml of urine) and heavy (≥ 50 eggs/10 ml of urine) [44].

In order to achieve a higher sensitivity in diagnostics, in selected schoolchildren stool and urine samples will be obtained on two consecutive days in Burkina Faso [45, 46]. For quality control, 10 % of all processed stool samples will be re-read under a microscope by independent laboratories [47]. Slides identified with discrepant results will be re-examined by the Institut de Recherches en Sciences de la Santé (IRSS) laboratory and Kirnetar Health Centre team until agreement has been reached.

### Collection of anthropometric indicators and measuring Hb levels

Selected schoolchildren will be subjected to anthropometric measurements according to SOPs, as described by WHO, using a digital scale and a height measuring board with a precision of 0.1 kg and 0.1 cm, respectively [48]. Individual z-score will be computed using the new WHO growth reference values for children and adolescents [49]. The nutritional status of schoolchildren will be classified as follows: a z-score within the interval of −3 standard deviation (SD) < z < −2 SD will be used to classify body-mass-index-for-age (BMIZ, thinness), height-for-age (HAZ, stunting) and weight-for-age (WAZ, wasting) as moderate undernutrition, and a z-score <−3 SD to define severe undernutrition. WAZ will only be used for children aged 8–10 years as reference data are not available beyond the age of 10 years [49]. Overweight will be classified as BMIZ >1.0 SD and obesity as BMIZ >2.0 SD [50].

The Hb level will be measured to determine anaemia prevalence. A finger-prick capillary blood sample will be taken, and Hb concentration measured using a HemoCue® 201+ testing device (HemoCue Hb 201+ System; HemoCue AB, Ängelholm, Sweden). Age-specific criteria will be used to identify anaemic children: Hb <11.5 g/dl for children aged 8–11 years and Hb <12 g/dl for children aged 12–14 years [51].

Additionally in Nepal, trained health care professionals will conduct clinical examinations for detecting clinical signs of nutritional deficiencies (e.g. dermatitis, bitot’s spot, dry and infected cornea, oedema, enlargement of liver, loss of peripheral sensation, angular stomatitis, pale conjunctiva, red inflamed tongue, swelling of the thyroid gland and bowed legs) [52].

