## Methods/Design

### Goal

The overarching goal of the studies within the frame of the VgtS project in Burkina Faso and Nepal is to address the current data gap on schoolchildren (aged 8–14 years) and to assess the effects of complementary school garden, nutrition and WASH interventions on schoolchildren’s health status, as assessed by a baseline and a 1-year follow-up survey through a range of previously identified nutrition, WASH and health indicators (Table 2).

**Table 2 Tab2:** Selected indicators for the two studies in Burkina Faso and Nepal

Objective	Indicator	Methods and tools	Survey module
*Individual level of child*			
To assess schoolchildren’s nutritional status at baseline and follow-up	Nutritional status (BMIZ, HAZ, WAZ and clinical signs of malnutrition)	Digital scale, height measuring board and clinical examination	Nutritional survey (module 1)
To assess the prevalence of anaemia in schoolchildren at baseline and follow-up	Anaemia based on haemoglobin levels < 11.5 g/dl for children aged 7 to 11 years and < 12 g/dl for those aged 12 to 14 years	HemoCue Hb 201^+^	Nutritional survey (module 1)
To assess the prevalence of intestinal parasitic infections in schoolchildren at baseline and follow-up	Presence and intensity of intestinal and urinary parasitic infections	Kato-Katz and formalin-ether concentration method for stool samples and centrifugation method for urine samples	Parasitological survey (module 2)
To assess schoolchildren’s nutrition and health knowledge, attitudes and practices (KAP) at baseline and follow-up	KAP related to nutrition and health	Questionnaire survey with schoolchildren Focus group discussions with schoolchildren In-depth interviews with school directors and teachers	Children’s health KAP (module 3)
*Environmental indicators*			
To assess drinking water quality of children’s drinking water recipients at baseline and follow-up	Presence of thermotolerant coliform bacteria and faecal streptococci	Portable DelAgua field kit and RAPID E. COLI 2 AGAR (coliform bacteria, *Escherichia coli*) and Bile Esculine Azide AGAR (faecal streptococci) tests	Water quality testing (module 4)
*Household level*			
* Demographic and socioeconomic data*			
To assess basic household socio-demographic and economic characteristics at baseline and follow-up	Caregiver’s age, educational level, occupational status, assets, food security	Household questionnaire	Household questionnaire survey (module 5)

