### Study sites and school selection

The studies will be conducted in Burkina Faso and Nepal. The study sites are located within the VgtS project sites, which were selected by the local VgtS country teams, following a set of criteria: (i) accessibility from the capital; (ii) availability of land for the school garden and continuous access to water at schools; (iii) coeducation of boys and girls in public schools; and (iv) willingness of the school principals and the community to participate.

In both countries, the study will be implemented in two different regions. In Burkina Faso, these are the Centre Ouest and the Plateau Central regions, both located in proximity to the capital Ouagadougou (30–180 km). The study sites in Nepal are the Dolakha and Ramechhap districts in the eastern part of the country, both located in proximity of the district headquarters Charikot (133 km) and Manthali (131 km), respectively.

The selection of the schools participating in the two studies is based on a three-stage sampling procedure of schools within the overall VgtS project sites. In a first step, about 100 schools fulfilling the aforementioned eligibility criteria were selected. In a second step, from these 100 schools, a sample of 30 schools were randomly chosen to be included in the VgtS school garden implementation and were randomly allocated to three groups, which receive the school vegetable garden interventions in 2014, 2015 and 2016, respectively. In a third step, out of the 30 VgtS project schools, a total of eight schools in Burkina Faso and 16 schools in Nepal were randomly selected to accommodate the sampling needs of the two complementary and slightly different study designs of Burkina Faso and Nepal (Fig. 1).

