### Study design

The two studies in Burkina Faso and Nepal are designed as cluster randomised trials with an equal number of schools randomly allocated to two core study arms (A, B) and with a cohort of children followed in two consecutive surveys, at baseline and 1-year follow-up. Two additional study arms are included in Nepal (C, D). The four study arms are designed as follows:arm A: school garden programme and complementary nutrition and WASH interventions;arm B: no interventions, i.e. controls;arm C: school garden programme without nutrition and WASH interventions; andarm D: nutrition and WASH interventions without the school garden programme.

Each arm comprises four schools. Figure 1 shows the study design with the different study arms for Burkina Faso and Nepal. In both countries, schools of arm A will receive the complementary school garden, nutrition and WASH intervention package starting in March 2015. In Nepal, the interventions from arms C and D will be implemented over the same period. In both countries, the control schools of arm B will benefit from the school garden intervention in the year following the interventions.

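### Anaemia is classified in both countries by haemoglobin cut-offs that vary by age only; if some Nepal schools lie high, prevalence and the between-country comparison are biased

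*Protocol article*

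**What the plan says.** The section on anthropometric indicators and Hb levels gives the purpose, "The Hb level will be measured to determine anaemia prevalence", and then the rule: "Age-specific criteria will be used to identify anaemic children", namely "Hb <11.5 g/dl for children aged 8–11 years and Hb <12 g/dl for children aged 12–14 years". Table 2, under Goal, repeats the thresholds: "haemoglobin levels < 11.5 g/dl for children aged 7 to 11 years and < 12 g/dl for those aged 12 to 14 years". The two statements differ in the lower end of the first age band (8 against 7 years). That does not affect this point, since enrolment starts at 8.

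One rule serves both countries, and altitude is not mentioned anywhere in the article. On location, Study sites and school selection says only that "The study sites in Nepal are the Dolakha and Ramechhap districts in the eastern part of the country", plus distances. No elevation is given for any school in either country.

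The article states these uses of anaemia status:
- prevalence at baseline and follow-up (Table 2);
- logistic models relating anaemia to risk factors (Data management and analysis);
- comparison of the study arms at the end of the intervention year (same section);
- comparative analysis of the data from the two countries (Discussion).

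Anaemia is not the outcome on which either sample size was based; that is intestinal parasitic infection (Sample size).

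**The concern.** Haemoglobin tends to be higher in people who live at altitude. This is general physiology and is not stated in the article. Where it applies, a fixed cut-off classes some truly anaemic children as non-anaemic, and the error goes in one direction only.

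Three of the stated uses have no protection from randomisation:
- **Descriptive prevalence.** Describing schoolchildren's health and filling a data gap are main aims. An under-count goes straight into the headline figure.
- **Between-country comparison.** If schools in one country carry an offset and those in the other do not, or carry a smaller one, the contrast mixes altitude with anaemia.
- **Risk-factor models.** School altitude could go together with water, sanitation or food conditions, and would then distort those associations.

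**Working it through.** The article gives no figure to reproduce: no expected anaemia prevalence in school-aged children, no haemoglobin distribution and no altitude. What follows is a sensitivity range on assumed inputs.

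**Inputs**
- From the article: cut-off 11.5 g/dl (younger band); four schools per arm; 8 + 16 = 24 schools; the same children measured at both surveys.
- Assumed: haemoglobin Normal, mean 12.5 to 13.0 g/dl, SD 1.0 to 1.2 g/dl; altitude offset c of 0, 0.2, 0.5 or 0.8 g/dl.

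**Step 1. Share of anaemic children missed.**
Counted prevalence = Φ((11.5 − mean)/SD). Adjusted prevalence = Φ((11.5 + c − mean)/SD). Share missed = 1 − counted/adjusted.

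The two extreme cases are:

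| c (g/dl) | mean 13.0, SD 1.0: adjusted | share missed | mean 12.5, SD 1.2: adjusted | share missed |
|---|---|---|---|---|
| 0 | 0.067 | 0 | 0.202 | 0 |
| 0.2 | 0.097 | 1 − 0.067/0.097 = 31% | 0.252 | 1 − 0.202/0.252 = 20% |
| 0.5 | 0.159 | 1 − 0.067/0.159 = 58% | 0.338 | 1 − 0.202/0.338 = 40% |
| 0.8 | 0.242 | 1 − 0.067/0.242 = 72% | 0.434 | 1 − 0.202/0.434 = 53% |

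Across non-zero offsets the share missed runs from about 20% to 72%. With no offset it is nil.

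**Step 2. The same question from a true prevalence p.**
Counted = Φ(Φ⁻¹(p) − c/SD). With p = 30% and SD 1.2 assumed, the counted prevalence is 24.5%, 17.3% or 11.7% for c = 0.2, 0.5 or 0.8. The shares missed are 1 − 24.5/30 = 18%, 1 − 17.3/30 = 42% and 1 − 11.7/30 = 61%. Widening the assumptions to p = 20–46% and SD 1.0–1.4 gives a range from 1 − 40.4/46 = 12% to 1 − 5.0/20 = 75%. The direction is stable; the size depends on the inputs.

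**Step 3. Comparison between arms.**
Four schools against four were randomised in 20,000 simulated draws. Each school's offset was drawn uniformly from 0 to a maximum, with true prevalence 30% and SD 1.2 in every school, so any difference is spurious.

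| maximum offset (g/dl) | mean arm difference | SD of arm difference |
|---|---|---|
| 0.2 | about 0 | 1.1 points |
| 0.5 | about 0 | 2.6 points |
| 0.8 | about 0 | 3.8 points |

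There is no systematic arm difference, only chance imbalance of about 1 to 4 percentage points (SD) at a single survey. A school's altitude is the same at both surveys, so its offset is already present at baseline and largely cancels in a baseline-adjusted comparison.

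**The case against.** The strongest objection is that the key premise is not in the document. No school altitude is given. The nearest hint, "due to the scattered locations and geographical constraints", explains why extra enumerators visit households in Nepal and says nothing about elevation. The offsets and the haemoglobin distribution are also assumed. This stands, and it is why the point is conditional.

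A reader might infer from the district names that Nepal anaemia will certainly be under-counted. The article does not support that: it does not describe the districts as hilly or high, and the effect could be nil.

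A reader might also infer that the arms will differ in anaemia because their schools differ in altitude. The article does not support that either. Schools are allocated at random, so the expected spurious difference is zero, and the same children are measured at baseline. The article plans a longitudinal analysis. How baseline enters it is not spelled out, and that may properly be left to an analysis plan.

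A further objection is that an article condenses the full protocol, and an adjustment may sit there, in a procedure or in the source cited for the cut-offs. That is possible. But the article prints the classification rule in full twice. Where the countries need different handling it says so: urine samples, the wet mount, clinical examinations and water testing. Someone following the printed rule would apply age-only cut-offs in both countries.

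Finally, anaemia is one of several indicators and not the sample-size outcome. This is correct, and it limits the weight of the point.

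**Conclusion.** The point holds in a conditional form. The printed rule classifies anaemia by age alone in both countries, with no altitude adjustment. If some Nepal schools lie high enough to raise haemoglobin, anaemia is under-counted there, and the descriptive prevalence, the risk-factor models and the between-country comparison are biased.

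Under the main assumed inputs, about 20% to 72% of anaemic children at such schools would be missed; none would be if no school is high. These figures illustrate sensitivity and do not estimate the effect in this trial. They rest on assumed offsets, an assumed Normal distribution and the younger age band's cut-off.

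The arm comparison is not seriously threatened. What remains is chance imbalance among four schools per arm, largely removed once baseline is taken into account. This is a cheap improvement to a non-primary indicator and not a flaw in the trial's main comparison.

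**What to change.** Record the altitude of each school once. State in advance which altitude adjustment will be applied to haemoglobin, and apply it in the analysis classification of anaemia at both surveys and in both countries. Report unadjusted prevalence alongside, so that the printed definition can still be followed. If an adjustment is already laid down elsewhere, say so where the cut-offs are given.

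The cost is 24 altitude readings, one line of analysis code and two prevalence figures to report instead of one. If all schools turn out to be low, the two figures agree and nothing is lost. The change concerns the analysis endpoint only and proposes nothing about who is examined or treated.

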### Drinking water quality assessment

In Burkina Faso, drinking water samples will be collected in sterile 250 ml bottles at the selected schools and community sources, children’s households and from their drinking water recipients to assess drinking water quality at source and point of use. Water samples will be randomly taken in 20 % of participating children’s households and in five community sources per study site (always including the school source). Water samples from children’s drinking water recipients brought to school will be randomly collected in 30 % of the children. Before analysis, the water samples collected will be preserved in cool boxes at 4 °C, and transferred to a nearby laboratory. The water samples will be analysed by membrane filtration for the presence/absence (PA) of thermotolerant faecal coliforms (TTC) as colony forming units per 100 ml of water (CFU/100 ml). Furthermore, *E. coli* and faecal streptococci as indicators for faecal contamination will be assessed by the use of the RAPID E. COLI 2 AGAR (coliform bacteria and *E. coli*; Bio-Rad Laboratories, Hercules, USA) and the Bile Esculine Azide AGAR (faecal streptococci; Bio-Rad Laboratories, Hercules, USA) tests according to WHO drinking water standards [53].

In Nepal, drinking water samples will be collected in 250 ml sterile bottles from the school drinking water source and children’s drinking water recipients, household and community water sources. Water samples will be collected at every school (*n*=16) and every child’s household (*n*=440). For the community sources, one water sample per study site will be taken from the principal water distribution channel of the community source (*n*=16). The water samples will be analysed *in situ* at the schools and households for turbidity, pH and chlorine residual using the *DelAgua* kit (Oxfam-DelAgua; Guildford, UK) using readily available SOPs [54]. If the concentration of free chlorine residual is greater than 0.2 mg/l (0.2 ppm) and the turbidity less than 5 turbidity units, the water samples will not be analysed for TTC [54]. If the results do not meet these criteria, water samples will be transported in cool boxes to the laboratory in Kirnetar Health Centre and stored in a refrigerator at 4 °C before analysis using the *DelAgua* kit. The water samples will be tested for CFU/100 ml according to WHO drinking water standards [53].

Quality control will be conducted with 10 % of all water samples collected by independent laboratories.

### Questionnaire survey with schoolchildren and their caregivers

The KAP survey was established with the guidelines and KAP manual provided by FAO, using standardised questions and amendments by the Swiss TPH research team [55]. Children’s caregivers will also be invited to respond to a questionnaire investigating sociodemographic, -economic, health and food security issues. The questionnaire surveys for children and their caregivers will be tablet-based using the Open Data Kit software [56].

